# International Care Bundle Evaluation in Cerebral Hemorrhage Research (I-CATCHER): Study protocol for a multicenter, batched, parallel, cluster-randomized trial with a baseline period

**DOI:** 10.1177/17474930251342888

**Published:** 2025-05-12

**Keywords:** Intracerebral hemorrhage, care bundle, blood pressure lowering, cluster trial, implementation, outcome

## Abstract

**Rationale::**

A care bundle approach to the management of spontaneous intracerebral hemorrhage (ICH) has been shown to benefit patients in low- and middle-income countries (LMIC), but uncertainty persists over the specific components and its applicability in high-income countries (HICs).

**Aims::**

An international collaborative initiative aimed at determining whether implementation of a care bundle improves functional outcome for patients with ICH in HIC.

**Methods::**

An international, multicenter, batched, parallel, cluster-randomized clinical trial focused on implementation and quality improvement for adults with spontaneous ICH ⩽ 24 h of symptom onset. The care bundle includes time- and target-based interventions: early intensive blood pressure lowering, hyperglycemia and pyrexia management, anticoagulation reversal, avoidance of do-not-resuscitate orders, repeat imaging, and referral pathways for intensive care and neurosurgery. An embedded process evaluation will assess the effectiveness and implementation of the care bundle.

**Sample size::**

A total of 110 hospitals with 3500 ICH participants is estimated to provide 90% power (α = 0.05) to detect a plausible treatment effect of 0.20 improvement in utility-weighted modified Rankin scale (UW-mRS) scores.

**Outcomes::**

The primary outcome is UW-mRS at 6 months. Secondary outcomes include death, functional status, and health-related quality of life. Implementation outcomes include adoption, fidelity, acceptability, sustainability, and integration.

**Discussion::**

We aim to provide reliable evidence to accelerate practice change for integration of a multifaceted ICH care bundle as a critical component of acute stroke care worldwide.

**Trial registration::**

Clinicaltrials.gov Identifier: NCT06429332.

## Introduction

Spontaneous intracerebral hemorrhage (ICH) accounts for up to 15% of acute strokes in high-income countries (HICs), but over half of all new stroke-related deaths and disability worldwide.^
1
^ Although a decreasing incidence of ICH has been observed in some countries, the burden of ICH is set to increase in Europe and other countries over the coming decades due to the aging of populations and lifestyle changes.^
2
^

The lack of proven treatments for ICH has created a sense of pessimism in many physicians, variable uptake of guideline-recommended treatments, and unnecessary use of early withdrawal of care in these patients.^
3
^ The devastating effects of ICH and the scarcity of randomized evidence to support single interventions have produced a nihilistic approach and over-estimates of adverse outcomes.^
4
^ Several prognostic variables in ICH include hematoma volume,^
3
^ level of consciousness,^
5
^ intraventricular hemorrhage,^
6
^ degree of hematoma expansion,^
7
^ and use of antithrombotic drugs.^
8
^ Management strategies that aim to limit hematoma growth include early intensive blood pressure (BP) lowering, reversal of anticoagulation, management of hyperglycemia, and targeted neurosurgery that includes the use of minimally invasive surgery (MIS),^
9
^ decompressive hemicraniectomy,^
10
^ and other approaches.

While efforts continue to define the role of individual interventions, evidence has emerged of the benefits of bundles of care in ICH.^3,11^ In particular, the third INTEnsive care bundle with blood pressure Reduction in Acute Cerebral hemorrhage Trial (INTERACT3) showed that the implementation of a systems of care approach that comprised a care bundle protocol for intensive BP lowering and other management algorithms for physiological control within several hours of ICH resulted in improved functional outcome.^
11
^ However, as most of the 121 hospitals which participated in INTERACT3 were located in low- and middle-income countries (LMICs), and the care bundle was dominated by intensive BP lowering, there may be uncertainty over the effectiveness, specific components, and fidelity of implementation of a care bundle in HIC.

Herein, we outline the protocol for the International Care Bundle Evaluation in Cerebral Hemorrhage Research (I-CATCHER) study that aims to evaluate the effectiveness of a relevant multifaceted care bundle for patients with ICH compared to usual standard care in hospitals located in HICs and some LMICs.

## Methods

### Study design

I-CATCHER is an international, multicenter, batched, parallel, cluster-randomized clinical trial with a baseline usual care period to evaluate a care bundle against current standard care in patients with spontaneous ICH. Participating sites are activated in batches, including a pre-determined size of 10 sites, allowing for consecutive enrollment of participants as additional hospitals join (Figure 1). Hospitals within a batch are randomized into two groups—intervention or control arm. The trial includes three phases: a baseline usual care phase; a randomized intervention phase; and a post-implementation period, once all sites have switched to the intervention (Figure 2). All participants are followed up for 6 months. Only data from the baseline and randomized phases will be used for the primary analysis. This study uses a type I hybrid design, which allows the simultaneous evaluation of the effectiveness of the intervention as well as its implementation in a broad range of healthcare settings.

**Figure 1. fig1-17474930251342888:**
[figure not shown]
Parallel cluster-randomized design with a baseline period. Participating sites are launched in batches according to readiness. A group represents the number of sites in each region that are cluster-randomized to either the intervention or the control arm.

**Figure 2. fig2-17474930251342888:**
[figure not shown]
Study schema.

### Population

The trial will include adults (age ⩾18 years) who present with spontaneous ICH. The inclusion and exclusion criteria are outlined in Table 1.

**Table 1. table1-17474930251342888:** Inclusion and exclusion criteria.

Inclusion criteria
• Adults (age ⩾ 18 years)
• NCCT or MRI-verified diagnosis of spontaneous ICH
• ⩽24 h from symptom onset or last seen well
Exclusion criteria
• Previous care limitation (i.e. previous DNR orders and/or limitations on life-sustaining treatment in an ICU setting, including any written patient directives regarding these limitations)
• End-stage comorbidity with short life-expectancy (<6 months, e.g. terminal cancer)
• ICH caused by brain tumor or cerebral venous thrombosis
• Clinical signs of brain herniation at first presentation
• Pregnant women beyond 22 gestational weeks may only be included after a thorough risk–benefit discussion with an obstetrician

DNR: do-not-resuscitate, ICH: intracerebral hemorrhage, ICU: intensive care unit, NCCT: non-contrast computerized tomography, MRI: magnetic resonance imaging.

### Randomization and blinding

An independent statistician will assign hospitals in a 1:1 ratio to the care bundle or usual care. Within each batch, participating sites will be stratified according to country and level of site (comprehensive tertiary with neurosurgeon services vs. secondary hospital without neurosurgeon services). Sites will be notified of their randomized group within 2 weeks of an agreed date before commencing the intervention. Treatment allocation is open label.

### Intervention

Implementation strategies will be used to introduce an active care bundle with time- and target-based metrics. Table 2 lists the components of the care bundle.

**Table 2. table2-17474930251342888:** Components of the care bundle intervention.

1. Reversal treatment of ongoing OAC, with either: 1. An elevated INR with the use of warfarin—treatment ⩽ 30 min after ICH detection and maintain INR target < 1.3; or 2. Use of a DOAC—treatment ⩽30 min with direct/indirect reversal agent
2. Early intensive BP lowering. 1. Systolic BP < 200 mm Hg after ICH detection: systolic target of 130–140 mm Hg should be achieved ⩽ 30 min of commencing treatment and maintained for the first 7 days. 2. Systolic BP ⩾ 200 and < 220 after ICH detection: systolic target of 160 mm Hg should be achieved ⩽ 30 min, and 130–140 mm Hg should be achieved ⩽ 60 min and maintained for the first 7 days. 3. Systolic BP ⩾ 220 after ICH detection: systolic target of 160 mm Hg should be achieved ⩽ 60 min and maintained for the first 7 days.
3. Pyrexia treatment: achieve a body temperature target < 37.5°C for 24 h from ICH detection
4. Hyperglycemia treatment: maintain a blood glucose level between 7 and 10 mmol/L for 24 h from ICH detection
5. No use of DNR or withdrawal of care for 48 h
6. Immediate (< 30 min) *referral* for intensive care if airway, breathing, and/or circulation are compromised during hospital stay (events related to the first 7 days of hospital stay are recorded in the eCRF)
7. Immediate (< 30 min) *referral* to neurosurgery if any of the following: 1. Large and/or rapidly evolving supratentorial ICH (> 20 ml volume) 2. Any IVH extension 3. Posterior fossa bleed, irrespective of volume 4. Suspicion of a vascular malformation, independent of volume or location 5. Altered consciousness or neurological deterioration since symptom onset or during hospital stay if related to ICH (events related to the first 7 days of hospital stay are recorded in the eCRF)
8. Repeat 6–12 h brain imaging if there is clinical deterioration or if the patient received OAC reversal treatment

BP: blood pressure, °C: degrees centigrade, DOAC: direct oral anticoagulant, DNR: do-not-resuscitate, ICH: intracerebral hemorrhage, INR: international normalized ratio, IVH: intraventricular hemorrhage, mmol/L: millimole per liter, OAC: oral anticoagulant.

For participants in the usual care group, decisions regarding their investigations, monitoring, and management are made by the attending clinical team.

### Clinical outcomes

The primary outcome is the utility-weighted modified Rankin scale (UW-mRS) score assessed at 6 months (180 ± 30 days). Secondary clinical efficacy outcomes will also be assessed at 6 months: (1) ordinal shift analysis of mRS; (2) death (mRS 6); (3) disability (mRS 3–5); (4) poor outcome (mRS 3–6); (5) health-related quality of life (HRQoL) based on the EuroQol 5-Dimension (EQ-5D); and (6) any readmission to hospital. Safety outcomes are (7) all serious adverse events (SAE) up to the study end; (8) SAEs ⩽ 7 days: episodes of severe hypotension (< 100 mm Hg) or hypoglycemia (< 4 mmol/L); and (9) SAE ⩽ 30 days: occurrence of any venous or arterial thromboembolic event. An SAE is defined as death; significant deterioration in a participant’s health characterized by a life-threatening illness or injury related to the study intervention (as stated above).

Centralized follow-up of participants will be undertaken by independent research staff blinded to treatment allocation. Follow-up clinical outcome assessors will contact the participant or a relative by telephone at 6 months. A health economic evaluation will be performed after study closure.

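### The SAE definition ties non-fatal events to the study intervention: read literally, none can count in usual care or at baseline, and either reading conflicts with safety outcomes (7) to (9)

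*Protocol article*

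**What the plan says.** The Clinical outcomes section lists three safety outcomes and labels each as SAEs:

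- (7) "all serious adverse events (SAE) up to the study end";
- (8) within 7 days, "episodes of severe hypotension (< 100 mm Hg) or hypoglycemia (< 4 mmol/L");
- (9) within 30 days, "occurrence of any venous or arterial thromboembolic event".

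The definition comes directly after the list. It has a fatal limb, "An SAE is defined as death", with no further condition. It also has a non-fatal limb: a significant deterioration in health "characterized by a life-threatening illness or injury related to the study intervention (as stated above").

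Under Intervention, the comparator is described only by who decides on care: "decisions regarding their investigations, monitoring, and management are made by the attending clinical team". Under Study design, every site starts with a usual care baseline phase, and "Only data from the baseline and randomized phases will be used for the primary analysis". Randomization and blinding states that treatment is open label. The Data safety monitoring board section says that the board sees unblinded safety outcomes and makes recommendations on continuing or stopping.

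**The concern.** A safety comparison between arms is meaningful only if an event is recognised by the same criteria in each arm. Here the non-fatal limb makes recognition depend on a link to the intervention under test, which only one arm receives, and only after randomization.

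If sites apply the sentence as printed, two distortions are possible, in opposite directions. With equal true rates, the bundle arm would show non-fatal SAEs and usual care would show none, which looks like harm. If relatedness is under-called at bundle sites, real harm could go uncounted. Sites may also read the sentence differently from one another, and an event never recorded at a control site may not be recoverable later. These data go unblinded to the monitoring board, so the wording matters during the trial as well as in the final report.

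**Working it through.** The article states no safety rate, SAE count or safety power, so there is no figure to reproduce. The check sets the definition against the outcomes it governs, under each of two readings.

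**Reading A: relatedness is a condition on each event.**

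| Site arm and phase | Study intervention given? | Deaths count? | Non-fatal SAE can meet the definition? |
|---|---|---|---|
| Control, baseline | No | Yes | No |
| Control, randomized | No | Yes | No |
| Bundle, baseline | No | Yes | No |
| Bundle, randomized | Yes | Yes | Yes, if judged related |

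Three of the four cells can contain only deaths. This contradicts *all* in (7) and *any* in (9), neither of which carries a relatedness limit. It also contradicts (8), whose events are set by thresholds that apply to any patient.

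**Reading B: the closing parenthesis points back to the event types in (8) and (9).** Control and baseline patients can then have countable events, and the imbalance between arms need not arise. Two conflicts remain:

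1. Non-fatal SAEs shrink to hypotension, hypoglycemia and thromboembolism, so (7) becomes deaths plus (8) and (9) and no longer covers all SAEs.
2. The limb still requires a life-threatening illness or injury. Outcome (8) is set by numerical thresholds and (9) accepts any thromboembolic event; neither requires a threat to life.

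So each reading contradicts something in the same paragraph.

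**Illustration of scale, Reading A only.** From the Sample size calculation section: 110 sites, randomized 1:1, with a mean of 16 participants per period, gives 110 / 2 × 16 = 880 per arm in the randomized phase. The article gives no rates, so the following are assumptions: a true non-fatal SAE rate of 5% to 20%, equal in both arms, with 10% to 50% of bundle-arm events judged related.

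- Low end: 880 × 0.05 × 0.10 = 4.4 events counted with the bundle, 0 with usual care; spurious risk difference 0.05 × 0.10 = 0.5 percentage points.
- High end: 880 × 0.20 × 0.50 = 88 events against 0; spurious risk difference 0.20 × 0.50 = 10 percentage points.

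If events counted regardless of relatedness, the expected difference under the same equal rates would be 0.

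**The case against.** The strongest reply is that this is one compressed sentence in a journal article, and that the literal reading is not the only one. The parenthesis follows closely on the named events and may simply mean the kinds of event that the bundle could cause. It may also point to treatments in the bundle, such as blood pressure lowering or anticoagulant reversal, which the attending team is free to use in usual care. On either view, control patients can have countable events. Outcomes (8) and (9) are specific, with their own thresholds and time windows, and a reader may reasonably let them prevail over a general definition. Death, poor functional outcome and readmission are collected with no relatedness condition, so serious harm would remain visible. The full protocol and the monitoring board's charter are not shown and may settle the matter.

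Much of this stands. A reader might infer that usual care and baseline cannot have any non-fatal SAE and that the safety comparison is biased by definition. The article does not support that, because it follows from Reading A alone and never applies to deaths. A reader might also infer that unblinded site staff decide relatedness. The article says only that allocation is open label; it does not say who makes the judgment.

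The reply does not rescue the sentence. Pointing to the event types leaves both conflicts under Reading B. Pointing to the treatments still makes counting depend on a causal judgment, against *all* in (7) and *any* in (9). Nor is this detail left to a fuller document: the article states a definition, and it disagrees with the outcomes listed just before it.

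**Conclusion.** The point holds as a defect in a stated definition. Under the literal reading, the non-fatal part of (7) is ascertained differently by arm and phase, and so are (8) and (9) if the condition is applied to them. Under the alternative reading, the definition is inconsistent with (7), and its life-threatening condition is inconsistent with (8) and (9). Deaths count equally everywhere.

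The size of any bias is unknown. The range of about 4 to 88 events against 0 rests on assumed rates, assumed shares judged related, and the literal reading. A reader might go further and take 5% of 880, or 44 events against 0, as the expected imbalance for hypotension. That is a worst case: it needs an assumed 5% rate, every bundle-arm event judged related, and the general definition overriding the thresholds in (8). The article establishes none of these.

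**What to change.** Reword the definition and align the eCRF guidance with it:

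- Remove the relatedness condition from the SAE definition.
- State that SAEs, and the events named in (8) and (9), are counted by the same event criteria in both arms and in both the baseline and randomized phases.
- Reconcile the life-threatening condition with (8) and (9), so that it is clear whether those events must meet it or stand as outcomes in their own right.
- Record relatedness as a separate field that does not decide whether an event counts, and state who assesses it.

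If the full protocol already does this, the published sentence should be corrected to match. The change alters no treatment, no sample size and no primary analysis. Its cost is a wording change and somewhat more event reporting at control sites and in the baseline phase.

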## Data safety monitoring board

An independent data safety monitoring board (DSMB) will review the safety and outcomes of the study, the quality of the trial conduct, monitor protocol adherence, and provide feedback to the Steering Committee on the conduct of the study as appropriate. The DSMB will meet 6-monthly to monitor the study progress and safety. A formal interim analysis will be performed by an independent statistician, blind to the randomized allocation, after 50 sites have reached data maturity. These data will then be reported to the DSMB for review of participant safety and outcomes as well as the quality of trial conduct. The DSMB will monitor unblinded safety outcomes and provide reports to the Steering Committee and recommendations in relation to continuation or stopping the study. A detailed DSMB charter will be made available that specifies the safety monitoring procedure and stopping rules.

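### Non-fatal SAEs outside the listed events are tied to relatedness to an intervention that usual-care patients do not receive, so this part of safety outcome (7) is not counted by one rule in both arms

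*Protocol article*

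**What the plan says.** All the relevant safety wording is in the Clinical outcomes section of the protocol article.

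- Outcome (7) is "all serious adverse events (SAE) up to the study end".
- Outcome (8) covers SAEs in the first 7 days: "episodes of severe hypotension (< 100 mm Hg) or hypoglycemia (< 4 mmol/L"). Outcome (9) covers SAEs in the first 30 days: "occurrence of any venous or arterial thromboembolic event". Neither item carries a causality condition.
- The general definition follows: "An SAE is defined as death; significant deterioration in a participant’s health" that is "characterized by a life-threatening illness or injury related to the study intervention (as stated above"). Death has no causality condition; the non-fatal limb has one.

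Three other sections bear on how this works in practice. Under Intervention, for the usual-care group, "decisions regarding their investigations, monitoring, and management are made by the attending clinical team". Study design describes the baseline phase as usual care too, and Randomization and blinding states that allocation is open label. Under Data safety monitoring board, "The DSMB will monitor unblinded safety outcomes", and the board advises on continuing or stopping the study.

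**The concern.** A between-arm safety comparison needs one counting rule for both arms. Here the non-fatal limb depends on a causal link to the study intervention. In the bundle arm that link can be asserted. In usual care, and in the baseline phase at every site, there is no study intervention for the event to be related to. The same episode of respiratory or renal failure could be an SAE at one hospital and not at another, solely because of the arm.

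The bias has a direction: it adds non-fatal events to the bundle arm only. The safety board would see it unblinded and could be asked to judge an excess that arises from the definition. The analysis plan cannot repair this later, because control events that sites never recorded as SAEs cannot be recovered.

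**Working it through.** **1. Which events are affected**

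| Event | Causality condition in the text? | Countable in bundle arm | Countable in usual care, read literally |
|---|---|---|---|
| Death | No | Yes | Yes |
| Listed hypotension or hypoglycemia, 7 days (8) | None in the item | Yes | Yes |
| Thromboembolic event, 30 days (9) | None in the item | Yes | Yes |
| Other non-fatal life-threatening event | Yes | If judged related | No |

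Only the last row is asymmetric.

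**2. Denominator**

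The sample size section gives 110 sites × 2 phases × 15 participants = 3300. Half are in the randomized phase: 110 × 15 = 1650. With 1:1 allocation this is 55 × 15 = 825 per arm.

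**3. Assumed rates**

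The documents state no SAE or death rates, so these are assumptions: the true rate of unlisted non-fatal life-threatening events is 8% in both arms (825 × 0.08 = 66 each). The share judged related is 10%, 25% or 50% in the bundle arm and zero in control. There is no true difference. The recorded bundle events are 66 × 0.10 ≈ 7, 66 × 0.25 ≈ 16 and 66 × 0.50 = 33, against 0.

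**4. Non-fatal unlisted events alone (Fisher exact, 825 per arm)**

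The design effect comes from the plan's ICC for the primary outcome: 1 + (15 − 1) × 0.05 = 1.7. Using it for SAEs is a further assumption. Counts and denominators are divided by 1.7 (825 / 1.7 ≈ 485).

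| Bundle vs control | p, clustering ignored | p, design effect 1.7 |
|---|---|---|
| 7 vs 0 | 0.015 | about 0.12 |
| 16 vs 0 | 0.00003 | about 0.004 |
| 33 vs 0 | 1.7 × 10⁻¹⁰ | about 3 × 10⁻⁶ |

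**5. Total SAEs, which is what outcome (7) names**

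Equal deaths are added to both arms: 15%, 25% or 35% of 825, which is 124, 206 or 289. Fisher exact p, clustering ignored:

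| Extra bundle events | Deaths 15% | Deaths 25% | Deaths 35% |
|---|---|---|---|
| 7 | 0.68 | 0.73 | 0.76 |
| 16 | 0.31 | 0.40 | 0.44 |
| 33 | 0.036 | 0.076 | 0.10 |

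At 25% deaths and 33 extra events the totals are 239 vs 206, or 29.0% vs 25.0%, a ratio of 1.16. Clustering would weaken all nine results.

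**6. A higher assumed event rate**

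With a 10% non-fatal rate and deaths of 15–35%, the chance of a nominally significant difference in total SAEs with no true effect is 24–37% at 30% attribution and 55–76% at 50%, ignoring clustering. With the 1.7 design effect it is 16–24% and 36–54%. At 10% attribution it is close to the nominal 5% (5–8% across both calculations).

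**7. Without the relatedness condition**

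Both arms record deaths plus all non-fatal events, and the expected difference under equal true risk is 0.

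**The case against.** The strongest reply is that the clause need not be read this way. Its closing back-reference may point to outcomes (8) and (9), making it shorthand for those listed events. The relatedness phrase may attach to injury only, not to illness. Usual-care clinicians may also use the same treatments, so similar complications can occur in control. The listed events cover foreseeable harms of blood pressure lowering, glucose control and anticoagulant reversal, and they carry no causality condition. The full protocol and the safety board's charter are not shown and may settle the matter.

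Part of this stands. The sentence is ambiguous, and the listed harms are not exposed to the problem as their own items are worded. But ambiguity does not protect outcome (7). If the clause limits non-fatal SAEs to the listed events, outcome (7) is not all SAEs; if it does not, relatedness governs the rest. Treatment chosen by a usual-care clinician is still not the study intervention.

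A reader might go further and infer three things that the documents do not support:

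- *That control SAEs are near zero, or deaths only, by definition.* Deaths count in both arms and so can the events in (8) and (9).
- *That a mortality benefit would hide non-fatal harm in the total.* Death is reported separately as secondary outcome (2), so equal totals with fewer deaths would show the non-fatal excess. Nothing says only one total will be presented.
- *That an unblinded clinician decides relatedness.* The article does not say who judges it. Open-label allocation means only that site staff know the arm.

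**Conclusion.** The point holds for the non-fatal, unlisted part of outcome (7). Read literally, that part is counted by different rules in the two arms and is biased toward an apparent bundle excess. It does not make the whole safety comparison uninterpretable: mortality and the listed harms can be counted alike in both arms, and the primary outcome is unaffected.

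The size depends wholly on assumed rates. For total SAEs the distortion is modest unless a large share of events is attributed to the bundle. For a non-fatal-only comparison it is severe: 16 against 0 remains nominally significant after allowing for clustering, although 7 against 0 does not. These figures rest on no attribution at all in control and on the literal reading of a condensed sentence. There is also a smaller inconsistency: outcomes (8) and (9) are called SAEs, yet a reading below their cut-offs, or any thromboembolic event, need not be life-threatening or related, and so may fail the definition that follows them.

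**What to change.** 1. In the SAE definition used for the between-arm comparison in outcome (7), remove the condition of relatedness to the study intervention.
2. State that the definition applies identically in both arms and in both the baseline and randomized phases.
3. Keep relatedness as a separate descriptive field in the eCRF that plays no part in deciding whether an event is an SAE.
4. Reconcile the general definition with outcomes (8) and (9): either state that these listed events count as SAEs in their own right, or present them as events of special interest outside the definition.

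Showing non-fatal SAEs apart from deaths in the safety table would help the reader, but it is an addition and not the core fix: a separate row counted under the present wording would carry the bias in full.

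The cost is a wording change and an eCRF field. The downside is that usual-care sites will report somewhat more non-fatal events.
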